### Ethical considerations

Ethical approval of the study protocol was given by the Central Committee on Research Involving Human Subjects and by the local accredited Medical Research Ethics Committee of the region Arnhem-Nijmegen, the Netherlands (reference number: 2013/354). This study is to be conducted in accordance with the International Conferences of Harmonization Good Clinical Practice Guidelines, the principles of the Declaration of Helsinki 1964 as modified by the 52nd WMA General Assembly, Edinburgh, Scotland, October 2000 including two notes of clarification on paragraph 29 and 30, and the local national laws governing the conduct of clinical research studies. An independent data and safety monitoring board has been formed to monitor patient safety and treatment efficacy during the trial.

## Discussion

The SCLEROCYST trial is designed to evaluate the additional effect of pasireotide on hepatic cyst diameter reduction in patients treated by AS. We hypothesize that complementary pasireotide treatment results in an augmented treatment efficacy. Multiple studies have shown that AS is an effective and safe method to reduce hepatic cyst volume [7,23,24]. However, cyst reduction is curtailed by fluid re-accumulation following treatment [10]. Fluid secretion by cyst-lining cholangiocytes is mediated by intracellular 3′-5′-cyclic adenosine monophosphate (cAMP). Increased levels of cAMP lead to activation of cystic fibrosis transmembrane conductance regulator (CFTR). Opening of these chloride channels results in chloride efflux, with a subsequent osmotic gradient facilitating water transport into the cyst cavity [17,25]. Somatostatin analogues inhibit cAMP by activating the somatostatin receptor (SSTR), and thereby reduce cholangiocyte fluid production [12,17,26]. Indeed, previous randomized clinical trials showed that both octreotide and lanreotide are capable of reducing cystic liver volume [27].

In the context of this study we want to evaluate whether these inhibitory mechanisms of somatostatin analogues can halt cyst fluid re-accumulation following AS. We have chosen to apply the multi-receptor-targeted, long-acting somatostatin analogue pasireotide (SOM230) [16]. This cyclohexapeptide has a high binding affinity to SSTR 1, 2, 3 and 5 which are all expressed on cholangiocytes [12]. Compared to conventional somatostatin analogues, pasireotide has a broader binding profile and a higher affinity to SSTR 1, 3 and 5. In a polycystic kidney disease rodent model pasireotide decreased intracellular cAMP, cholangiocyte proliferation and expansion of hepatic cysts more effectively than octreotide [17]. Pasireotide is approved in the European Union and United States for the treatment of Cushing’s disease, and is currently being investigated for treatment of other diseases such as acromegaly and neuroendocrine tumors. Two formulations of pasireotide are available: an immediate release and a one-month depot formulation. To ensure adequate pasireotide levels and optimize patient adherence, we have chosen to administer the LAR formulation of pasireotide. A previous pharmacokinetic study of pasireotide LAR in healthy volunteers showed that pasireotide levels reached a peak (*t*_max_) around 20 days following administration [18]. Therefore, to secure adequate levels subsequent to AS, a first injection will be administered two weeks prior to AS, followed by a second injection two weeks following AS.

The strength of this study is its design: a randomized, double-blind, placebo-controlled trial. This will minimize confounding of results. Further, this study is powered on a clinical relevant difference of 50% in the pasireotide arm compared to the expected 30% cyst diameter reduction in the control arm. We believe that a statistical significant finding will have direct implications for future AS treatment. Smaller differences between arms will not be detected in view of power issues. Nevertheless, given the additional costs and potential side effects of pasireotide, we believe that a strong improvement over conventional AS is needed to justify the implementation of this combination treatment. Finally, with this study we hope to achieve a better understanding in the pathological mechanisms behind hepatic cyst development and fluid re-accumulation following AS.

This study has several limitations. First, the effect of treatment will be measured by ultrasonography. Since we will perform cyst measurements within short intervals we have selected ultrasonography as the most appropriate imaging modality to avoid exposure to radiation (from computed tomography scans) and high costs (from magnetic resonance imaging). However, ultrasound measurements are operator-dependent and are therefore susceptible to bias. To minimize biased results, we have added several safety measures. All measurements will be performed according to standard operating procedures and will be executed in triplicate. Moreover, all measurements will be performed by the same investigator who is blinded for treatment allocation. In addition, a second, blinded independent investigator will repeat all measurements. Second, in this study sclerotherapy will be performed with 100% ethanol. Multiple sclerosing agents are in use for AS ranging from ethanol to tetracycline antibiotics, polidocanol, ethanolamine oleate or hypertonic saline [8,28-32]. This might limit the generalization of our findings. On the other hand, ethanol is cheap, widely available and the clinical experience with this agent is large. Finally, AS will be performed by a number of interventional radiologists, theoretically introducing performance bias. Nevertheless, AS is a protocol procedure and large differences in treatment outcome between interventional radiologists are not to be expected.

To summarize, the SCLEROCYST trial is designed to evaluate the additional effect of a somatostatin analogue combined with AS. We aim to reduce fluid re-accumulation following treatment leading to increased cyst diameter reduction and symptomatic relief.

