### Sample size considerations

Recent data showed that patients treated by AS have a mean diameter reduction of 29.7 ± 19.76% after four weeks [23]. By adding pasireotide, we want to establish a decrease in cyst diameter of 50% after four weeks. A sample size of 15 patients per arm, leading to a total of 30 patients, is required to be able to obtain a significant difference between the two groups (power: 80%; α: 0.05). Taking into account the possibility of 10% protocol violators and/or dropouts, we aim to include 17 subjects per arm, giving a total of 34 patients.

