### Statistical analysis

Intention-to-treat (ITT) analyses will be used for all clinical outcome variables. The ITT sample includes all patients who received at least one dose of study medication. In addition, we will carry out a parallel analysis on the per-protocol treated population. This sample is defined as all patients who have received both injections, AS and all ultrasound measurements. The primary outcome of this study is the proportional (%) change in cyst diameter of the treated hepatic cyst four weeks after AS, as measured by ultrasound. The mean diameter of each orthogonal diameter measured by the blinded primary investigator will be used for analysis. Subsequently, we will calculate a mean diameter from the three mean orthogonal diameters. Proportional change will be calculated by dividing the reduction of mean cyst diameter at four weeks by mean cyst diameter at baseline, multiplied by 100. Depending on distribution, values will be presented as mean ± SD or as median ± interquartile range. Consequently, differences between the treatment and placebo arm will be calculated using the independent student’s t-test or the Mann-Whitney U test, respectively. Absolute reduction and volume reduction will be presented and analyzed similar to data for the primary endpoint. Cyst recurrence will be compared between both groups using Fisher’s exact test. The cyst diameter measurements from the second blinded investigator will be used as a control to evaluate intra- and interobserver variability by performing a Bland-Altman analysis. Symptoms of the GIS-questionnaire will be dichotomized (0 to oneversus two to six) and compared between the treatment and placebo arm using the chi-square test. Health-related quality of life domain scores and component scores (SF-36) will be compared between both arms using the Mann-Whitney U test. Frequency tables will be compiled for (serious) adverse events classified according to the standard World Health Organization - Adverse Reaction Terminology (WHO-ART) Body System Dictionary and preferred terms. All statistical analyses will be two-sided, with a critical significance level of 5%.

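### The Discussion says differences below the powered 20 points will not be detected; on the plan's own figures many would be, so significance alone does not show the strong improvement asked for

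*Protocol article*

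**What the plan says.** Under Sample size considerations, the protocol article takes from earlier data that "patients treated by AS have a mean diameter reduction of 29.7 ± 19.76% after four weeks". It sets the target as follows: "By adding pasireotide, we want to establish a decrease in cyst diameter of 50% after four weeks". The error rates are given as "power: 80%; α: 0.05". The result is 15 evaluable patients per arm, raised to 17 per arm for 10% violators or dropouts. Statistical analysis specifies a two-sided 5% comparison of the arms by t-test, or by Mann-Whitney U if the distribution calls for it.

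The Discussion restates the target as 50% against an expected 30% and calls that difference clinically relevant. Three statements follow in order:

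- on what a positive result would mean: "We believe that a statistical significant finding will have direct implications for future AS treatment"
- on effects that fall short of the target: "Smaller differences between arms will not be detected in view of power issues"
- on the benefit required, because of cost and side effects: "we believe that a strong improvement over conventional AS is needed to justify the implementation of this combination treatment"

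**The concern.** The middle statement treats the difference used for sizing as the smallest difference the trial can find. These are separate quantities. The sizing difference is the true effect at which the test succeeds 80% of the time. Smaller true effects succeed less often, but not never, and the observed difference needed for p<0.05 is well below the sizing difference.

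The position of the sentence makes this matter. If nothing under 20 points could reach significance, any significant result would show a large benefit, and the statements before and after would fit together. Since smaller effects can reach significance, they do not. The planned test is against a zero difference, and the article ties significance to no particular size of benefit. At stake is what a significant result may be said to show about a treatment whose cost and side effects the authors themselves weigh against its benefit.

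**Working it through.** **Inputs.** From Sample size considerations: control mean 29.7%, SD 19.76 points, target 50%, power 80%, alpha 0.05, n = 15 evaluable and 17 enrolled per arm. From Statistical analysis: two-sided test, independent t-test. Assumption: the same SD in both arms.

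**1. The plan's own sample size.** Difference = 50 − 29.7 = 20.3 points. By the normal approximation, n = 2 × (1.960 + 0.842)² × 19.76² / 20.3² ≈ 14.9, so 15 per arm. Allowing for dropout, 15 / 0.90 = 16.7, so 17 per arm. Both stated figures reproduce. (By the noncentral t distribution, power at 15 per arm is 77.5% and 16 per arm would be needed. This is a small difference and not the point here.)

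**2. Smallest significant observed difference.** This is t(0.975, 2n−2) × SD × √(2/n).

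- n = 15: 2.048 × 19.76 × √(2/15) = 2.048 × 7.215 = 14.8 points
- n = 17: 2.037 × 19.76 × √(2/17) = 2.037 × 6.778 = 13.8 points

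These are 73% and 68% of 20.3. At the threshold, the 95% confidence interval runs from 0 to twice the threshold: 0 to 29.6 points (n = 15) or 0 to 27.6 points (n = 17).

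**3. Power for true differences.** Noncentral t with 2n−2 degrees of freedom and noncentrality = true difference / SE, where SE is 7.215 or 6.778:

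| True difference (points) | 15 per arm | 17 per arm |
|---|---|---|
| 10 | 26.8% | 29.9% |
| 15 | 51.9% | 57.4% |
| 18 | 67.3% | 73.1% |
| 20 | 76.3% | 81.6% |
| 20.3 | 77.5% | 82.7% |

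**4. Size of estimate among significant results** (simulation, 200,000 trials per setting). If the true difference is 20.3, 33% (n = 15) to 37% (n = 17) of significant results have an estimate below 20 points. If it is 15, the share is 53% to 60%.

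**5. Sensitivity to the SD.** The threshold at 15 / 17 per arm is 11.2 / 10.5 points for an observed SD of 15, and 18.7 / 17.5 for an SD of 25. At 15 per arm it reaches 20 only when the SD is 20 / (2.048 × √(2/15)) ≈ 26.7.

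**The case against.** The best defence is that the sentence speaks of power, hence of true differences, and is shorthand for *not reliably detected*. On that reading the 14-15 point threshold, which concerns the observed difference, does not by itself contradict it. For small effects the shorthand is fair: power is about 10-11% at a true 5 points and 27-30% at 10. It fails closer to the target, where a true 15 points has a better than even chance of significance and 18 points about two chances in three or more. The text carries no qualifier.

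It can also be said that the paragraph separates significance from clinical justification, because it goes on to require a strong improvement. That stands in part. The requirement is the right one, but the article does not say how a result would be held against it.

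Two stronger readings are tempting, and the article supports neither.

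- A reader might infer a formal rule under which p<0.05 leads to a recommendation. There is none. The statement about implications is a belief expressed in the Discussion, it is not linked by any *because* to the sentence on smaller differences, and neither the endpoint nor the analysis section contains such a rule.
- A reader might infer that a non-significant result would be taken to exclude a relevant benefit. The article nowhere says so.

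**Conclusion.** The point holds as a minor one. The statement that smaller differences will not be detected is incorrect as written, by the margins shown above. A significant result could come with an estimate of 14 or 15 points and an interval reaching down to about zero. That would be evidence of some effect, but not of the strong improvement the authors require.

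The figures assume a common SD equal to the planned 19.76, a t-test, and 15 to 17 analysed patients per arm. The threshold moves with the observed SD, and a Mann-Whitney analysis has no fixed threshold in mean points. Neither limit makes the sentence true. The endpoint, sample size, test and significance level are not in question.

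**What to change.** In the Discussion, replace the sentence with one such as: *With 15 evaluable patients per arm, differences smaller than 20 points will be detected with less than 80% power.* The reference to 15 per arm is useful because, with all 17 analysed, power at exactly 20 points is 81.6%.

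Then add that implications for practice will be judged from the estimated difference and its 95% confidence interval in relation to the 20-point difference, not from p<0.05 alone. A significant result with an estimate clearly below 20 points would be described as evidence of some effect, not of the strong improvement.

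Two over-corrections should be avoided:

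- **Requiring the lower confidence limit to exceed 20 points.** This would need an observed difference of about 34-35 points (20 + 13.8 or 20 + 14.8). The chance of that is about 3% if the true difference is 20.3.
- **Calling a significant result inconclusive only because its interval includes 20.** An on-target result of 20 points at 15 per arm has an interval of about 5 to 35 (20 ± 14.8) and would be mislabelled.

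The cost is a few sentences. Test, sample size and conduct stay as they are; only the claim that may rest on a significant result becomes narrower.

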## Trial status

The trial is currently ongoing. Recruitment and inclusion of patients started in April 2014.

## Abbreviations

ALT: Alanine aminotransferase
ALP: Alkaline phosphatase
AS: Aspiration sclerotherapy
AST: Aspartate aminotransferase
cAMP: 3′-5′-cyclic adenosine monophosphate
CFTR: Cystic fibrosis transmembrane conductance regulator
FBS: Fasting blood sugar
GGT: Gamma-glutamyl transpeptidase
GIS: Gastrointestinal symptoms questionnaire
INR: International normalized ratio
LAR: Long-acting release
MDRD: Modification of diet in renal diseases
PLD: Polycystic liver disease
PLD-Q: Polycystic liver disease questionnaire
SF-36: Short form 36 health survey
SSTR: Somatostatin receptor
TB: Total bilirubin
QTc: Corrected QT interval
